#### Decisional regret

During the same telephone call, the research assistant will assess the patient's decisional regret using the Decisional Regret Scale. The Decisional Regret Scale is a 5-item scale with efficient psychometric properties that correlates strongly with decision satisfaction and overall quality of life [22].

#### Quality of life

Patients’ quality of life will be assessed, immediately before and two weeks after the clinical encounter. In both cases, the research assistant will use the Short Form-12 questionnaire (SF-12V2 Health survey) [23] to measure the patient's general health status from his/her point of view. This questionnaire evaluates eight elements commonly held to represent health status: physical fitness, role functioning, pain, general health, vitality, social abilities, and emotional and mental health.

#### Intention to engage in SDM in future consultations dealing with antibiotics for ARIs

This intention on the part of FPs and their patients will be assessed by questionnaire in reference to the Theory of Planned Behaviour [24]. Composed of 15 items scored with a 7-point Likert scale, the questionnaire covers the theory's constructs, namely, attitudes, subjective norm, perceived behavioural control, and intention. Patients will complete this questionnaire before and 2 weeks after the clinical encounter; physicians will complete it once during the baseline data collection period and once again after the post-intervention data collection period. From a theoretical perspective, the questionnaire will ensure that we understand what underlying mechanisms should be considered when developing interventions to apply SDM in primary care.

### Other variables (potential effect modifiers)

#### Sociodemographic characteristics

Before the clinical encounter, patients will be assessed in terms of the following sociodemographic characteristics: age, gender, highest educational degree, employment, annual household income, size of household, marital status and health. FPs' characteristics will also be determined before the clinical encounter, during the first data collection period. We will assess FPs' age, number of years in practice, gender, number of formal years of education, other degrees, participation in committees, continuing professional development activities, and anxiety about uncertainty and disclosing uncertainty to patients [25,26].

### Data collection procedures

There will be two data collection periods: pre-intervention (baseline) and post-intervention. We will record data for FPs once during the baseline phase. Patients' characteristics will be recorded before their clinical encounter with the physician. After the clinical encounter, the patient and the physician will independently complete self-administered questionnaires that will assess both the decision that had been made (the primary outcome) and decisional conflict. Both the patient and the physician will also assess independently if SDM occurred. Patients will be contacted by phone two weeks after the clinical encounter to complete a short interview (adherence to the decision, consultation for the same reason, decisional regret, quality of life, and intention to engage in SDM). FPs' intention to engage in SDM regarding the use of antibiotics for ARIs will be recorded at baseline and again at the end of the study.

### Sample size and analysis

The primary outcome is whether or not patients report a decision for immediate use of antibiotics for ARI after an index consultation. In the pilot RCT, immediate use of antibiotics was 56% in the experimental group and 54% in the control group at baseline. We assume that the minimum clinical significance for an absolute reduction of immediate use of antibiotics is 20%. In order to detect a reduction from 60% to 40% with 80% power, at a 5% significance level, one would require a total of 194 patients in an individually randomized two-group trial. To take account of the clustering of participants within FPTU (unit of randomisation), we used an intracluster correlation coefficient (ICC) of 0.02 estimated from our pilot cluster RCT [15,16]. Therefore, we will need 288 patients to have the same power as an individually randomized trial, that is, 24 patients per cluster assuming that all 12 FPTUs (clusters) will participate. In order to compensate for loss due to follow up and missing data (as observed in our pilot RCT), we will recruit 350 patients at each data collection period, 175 patients per group per period.

We will perform descriptive statistical analysis of socio-demographic characteristics in order to assure the comparability of both groups (intervention and control). Potentially confounding variables will be introduced as covariates in statistical modelling analyses. Multilevel modelling will be used in order to take the hierarchical structure of the data into account by specifying random effects at each of the three levels: FTPU, FP and patient. For each outcome analysed, according to the type of variables (continuous or categorical), the goodness of fit and the assumptions of each model will be assessed. Statistical analysis will be performed using the SAS statistical package (SAS Institute Inc. 2005. SAS OnlineDoc^® ^9.1.3. Cary, NC: SAS Institute Inc.) and the MLM software MLwiN 2.10 Beta.

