In 2008, we completed a pilot clustered randomized controlled trial (RCT) studying antibiotics prescriptions for ARIs in primary care [15]. We randomized four family medicine groups (FMGs) to an intervention group (two FMGs, 18 FPs, and 173 patients) or to a control group (two FMGs, 15 FPs, and 147 patients). We found that FPs' exposure to DECISION**+**, a multifaceted intervention for implementing SDM in medical practices that included training, reminders and feedback, was associated with a decrease in decisions for "immediate antibiotics" compared to decisions for "delayed/no antibiotics" (49% vs. 33% absolute difference = 16%; p = 0.08 and relative risk = 0.69; 95% CI: 0.47-1.03). By "immediate antibiotics," we refer to the patient's decision, made during the consultation, to use antibiotics immediately to treat the ARI. Associated with the main outcomes of this pilot trial that demonstrated the feasibility and acceptability [16], we are now conducting a large clustered RCT of a modified version of DECISION+, DECISION+2. The proposed trial will be the first RCT with sufficient statistical power to assess the impact of DECISION+2 on ARI patients reporting a decision to use antibiotics immediately. This information will inform strategies that cause the parties to work together to improve the clinical decision-making process for the treatment of ARIs. In so doing, the RCT will address the problem of antibiotic overuse for ARIs in primary care and eventually improve population health.

The proposed RCT is based on our conceptual framework [17] and the results of the pilot RCT [15,16]. Its first objective is to evaluate how DECISION+2 impacts the proportion of ARI patients reporting a decision to use antibiotics immediately. The other objectives are to estimate the impact of DECISION+2 on 1) the decisional conflict scores of physicians and their patients and the level of agreement between their scores, 2) perception of patients and physicians that SDM occurred, 3) patients' adherence to the decision made, 4) consultation for the same reason, 5) patients' decisional regret, 6) patients' quality of life, and 7) physicians and patients' intention to engage in SDM in future clinical encounters dealing with antibiotics for ARIs.

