## Discussion

This RCT will be the first study with enough statistical power to assess the impact of DECISION+2 on reporting a decision for the immediate use of antibiotics for ARIs in the context of FPTUs. We expect DECISION+2 to foster SDM in consultations between FPs and their patients. The innovative approach proposed in this trial recognizes that translating and exchanging knowledge and implementing evidence in clinical practice result from a complex interplay of interpersonal elements that influence the clinical encounter. By revealing as yet unknown mechanisms that underlie knowledge transfer in the clinical context, DECISION+2 has the potential to foster new knowledge transfer strategies that optimize drug prescriptions.

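### The 80% power at 5% significance stated for 288 patients makes no allowance for only 12 randomised clusters; with a test that holds 5%, power is about 73-77%

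*Protocol article*

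**What the plan says.** Under Sample size and analysis, the protocol article sets the target: "In order to detect a reduction from 60% to 40% with 80% power, at a 5% significance level". It first gives the size without clustering: "one would require a total of 194 patients in an individually randomized two-group trial". For clustering, "we used an intracluster correlation coefficient (ICC) of 0.02 estimated from our pilot cluster RCT", which leads to "we will need 288 patients to have the same power as an individually randomized trial, that is, 24 patients per cluster", on the assumption that all 12 units take part. Recruitment is then raised to 350 per data collection period (175 per arm) to cover losses and missing data; no loss rate is given.

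The unit of randomisation is the FPTU (Allocation of participants to trial groups). The planned analysis is a multilevel model with random effects for FPTU, physician and patient.

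Two other places rely on the power figure. The Background says: "The proposed trial will be the first RCT with sufficient statistical power to assess the impact of DECISION+2 on ARI patients". The Discussion says: "This RCT will be the first study with enough statistical power to assess the impact of DECISION+2".

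**The concern.** A design effect corrects the variance of the treatment comparison for clustering. It does not correct for how poorly that variance is estimated when few clusters are randomised. With 12 FPTUs in two arms, the between-FPTU variance is estimated on 12 - 2 = 10 degrees of freedom. The two-sided 5% critical value is then 2.228, not 1.96. The sample-size paragraph contains no step for this: no t-based critical value and no added cluster.

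The stated pair of 80% power and 5% significance is therefore in doubt at the stated size of 288. If the pair fails, a null result could be read as somewhat stronger evidence against a 20-point reduction than the design supports. If the model is instead tested against 1.96, the false-positive rate exceeds the stated 5%.

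**Working it through.** **Inputs.** From Sample size and analysis: 60% versus 40%, 80% power, 5% significance, ICC 0.02, 12 clusters of 24, recruitment of 350. Assumed here: a two-sided test (only this reproduces 194; one-sided gives 154), 6 FPTUs per arm, equal cluster sizes, and comparison of the post-intervention period only.

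**Step 1: reproduce 194.** Pooled two-proportion formula, without continuity correction:
n per arm = [1.96 × √(2 × 0.5 × 0.5) + 0.842 × √(0.24 + 0.24)]² / 0.20² = 96.9, so 97 per arm and 194 in total. It matches.

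**Step 2: reproduce 288.** Solve 12m = 194 × [1 + 0.02(m - 1)]:
m = (194 × 0.98) / (12 - 194 × 0.02) = 190.12 / 8.12 = 23.4, rounded up to 24, and 12 × 24 = 288. It matches. The design effect at 24 per cluster is 1 + 23 × 0.02 = 1.46.

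**Step 3: power at 288 by normal theory.** The standard error of the difference is √(0.48 × 1.46 / 144) = 0.0698 (unpooled) or √(0.50 × 1.46 / 144) = 0.0712 (pooled). Power is Φ(0.20/0.0698 - 1.96) = Φ(0.907) = 81.8% unpooled. With the pooled standard error under the null it is Φ[(0.20 - 1.96 × 0.0712)/0.0698] = 80.7%. This is the plan's 80%.

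**Step 4: power at 288 on 10 degrees of freedom.** Noncentral t, critical value 2.228, noncentrality 0.20/0.0698 = 2.87 or 0.20/0.0712 = 2.81: power 73.4% or 71.7%.

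**Step 5: simulation, 6 versus 6 clusters.** Beta-binomial data with ICC 0.02. The logistic model has a random intercept for FPTU only; the physician level is left out. Ranges span separate simulation runs.

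| Test | Power, 24 per FPTU (288) | Power, 29 per FPTU (348) | Type I error |
|---|---|---|---|
| Cluster-level t-test, 10 df | 72-74% | 77-78% | about 5% |
| Cluster-level comparison against 1.96 | 80% | 84-85% | 7.5-8% |
| Random-intercept logistic model, 10 df | 76-77% | 80-81% | 4-5% |
| Random-intercept logistic model against 1.96 | about 82-83% | about 87% | 7-8% |

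As a cross-check, the two-sided probability of exceeding 1.96 under a t distribution with 10 df is 7.8%.

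**Step 6: all 350 analysed.** 350/12 = 29.2 per FPTU, design effect 1.563. The noncentral t gives 76.9% (pooled) to 78.6% (unpooled). The model reaches 80-81% at 29 per FPTU (Step 5).

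**The case against.** The strongest reply is that the cluster-level t-test is not the planned analysis. A multilevel model is planned, and with a 10-df reference it loses only about 3 to 4 points at 288. In addition, the primary outcome is collected right after the consultation, not at the two-week call, so follow-up loss does not remove it and the number analysed may come close to 350. At that number a model of the planned kind reaches about 80-81% with 5% significance. This reply stands, and it is why the shortfall must be given as a range. It does not rescue the statement as printed, which attaches 80% to 288 and reserves the remaining 62 patients for losses and missing data.

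A reader might infer more than the document supports:

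- **An arithmetic slip.** There is none: 194 and 288 both reproduce. The objection is to the reference distribution.
- **Power of about 74% under the planned analysis.** That figure belongs to a cluster-level or formula-based t-test.
- **80% power and 5% significance can never hold together.** This is true at 288, but not if nearly all 350 are analysed with the model.
- **A much larger deficit** from a higher ICC, unequal clusters, fewer units or physician-level clustering. The document gives no values for such departures, and participation of all 12 units is openly stated as an assumption.
- **Inadequate power for the pilot's 16-point difference (49% versus 33%).** The plan sets 20 points as its minimum important reduction and makes no power claim for 16.

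Adjustment for covariates could recover some power, but the calculation claims no such gain and the document gives no figure for it.

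**Conclusion.** The point holds in a limited form. At 288 analysed patients, the stated 80% power and 5% significance are not both met. A valid 5% test has about 72-74% power (cluster-level t-test) or about 76-77% (random-intercept logistic model on 10 df), a shortfall of about 3 to 8 points. If nearly all 350 are analysed, power is about 77-81% and the shortfall can disappear.

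This rests on an ICC of exactly 0.02, equal clusters, 6 units per arm, a two-sided test and no physician-level variance in the simulated model. The design is not invalidated. A protocol article may leave the degrees-of-freedom method to the analysis plan, so its absence is not the fault; the fault is a stated figure that makes no allowance for 12 clusters. Severity: moderate.

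**What to change.** 1. In Sample size and analysis, restate the power for 60% versus 40% with 12 FPTUs, ICC 0.02 and a two-sided 5% test on 10 df as about 73-77% at 288 analysed, and about 77-81% if all 350 are analysed. Name the test behind each figure: the lower end is the cluster-level t-test, the upper end the random-intercept logistic model.
2. State that the comparison between arms will use a small-sample reference with 10 df and not 1.96.
3. Qualify the claims of adequate power in the Background and the Discussion to match.

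The cost is a few sentences and a slightly less favourable stated power. No extra patients, recruitment quota per unit or sensitivity table is required.

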## Discussion

This RCT will be the first study with enough statistical power to assess the impact of DECISION+2 on reporting a decision for the immediate use of antibiotics for ARIs in the context of FPTUs. We expect DECISION+2 to foster SDM in consultations between FPs and their patients. The innovative approach proposed in this trial recognizes that translating and exchanging knowledge and implementing evidence in clinical practice result from a complex interplay of interpersonal elements that influence the clinical encounter. By revealing as yet unknown mechanisms that underlie knowledge transfer in the clinical context, DECISION+2 has the potential to foster new knowledge transfer strategies that optimize drug prescriptions.
